### Statistical analyses

Descriptive and summary statistics will be calculated by treatment group and stratum (pre-hospital and emergency department region) for baseline characteristics. Continuous data will be summarised as means (standard deviations) or medians (interquartile ranges) for non-normal data and categorical data by counts and proportions. The number of screened patients who fulfilled study inclusion criteria and the number included in the primary and secondary analyses as well as all reasons for exclusions in primary and secondary analyses will be reported.

The main primary and secondary analyses will follow an ITT approach to define the full analysis patient set, based on all randomly assigned patients after the eight-patient run-in period, except those withdrawing consent for use of all trial data and those not fulfilling inclusion criteria and never receiving the intervention [20, 29].

The early intervention design of the POLAR study specifically anticipates incomplete adherence to assigned cooling treatment in the complex clinical context of the study cohort. It is expected that the main reason for incomplete compliance with cooling will be due to the effects of alcohol or other drugs confounding assessment of TBI severity at the time of randomisation, leading to inclusion of patients with impaired consciousness not due to severe TBI for whom ongoing cooling may be clinically unwarranted. Other anticipated reasons include extracranial trauma and coincident haemorrhage for which cooling may be at least temporarily undesirable in the context of a patient’s overall clinical condition.

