#### Dose effect / Intensity of cooling

Intensity of cooling in intervention arm patients will be categorised according to the time after randomisation to first reach one of two core temperature thresholds, being the limit of mild hypothermia 35 °C [9] and also 34 °C as an indicator of more intense [6] cooling below 35 °C towards 33 °C. Cooling intensity categories are defined as never achieving hypothermia and tertiles of time in those reaching hypothermia. Primary and secondary outcomes of patients in these intensity categories will be compared across categories and to standard care patients.

Differential effects of cooling on the primary and secondary outcomes will be assessed according to: (1) Marshall computed tomography (CT) scan classification V; and (2) Marshall V or VI. These will be performed using appropriate covariate by treatment interaction terms in the relevant regression models.

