##### As-treated and per-protocol analyses

POLAR will repeat the primary and secondary trial outcomes in two pre-defined exploratory analysis sets: (1) the subset of compliant patients assigned to cooling compared to all patients assigned to the control (‘per-protocol’ analysis); and (2) according to the actual treatment received (‘as-treated’ analysis) [7].

The per-protocol analysis subset will comprise control and intervention patients who are demonstrated retrospectively to have suffered a severe TBI, thus excluding those with initially low GCS < 9 not due to severe head injury but rather associated with transient influences, such as alcohol or drug effects.

For analytic purposes, the differential ‘dose’ of early cooling received by each patient will be summarised as the area (degree × hours) under the protocol-defined cooling baseline value of 35 °C within 72 h of randomisation. Each individual’s AUC will be estimated by the linear trapezoidal method [41] applied to temperature data ignoring missing values. Early death or loss to follow-up within 72 h of randomisation will by definition reduce the observed dose of cooling received by such patients. The intensity of cooling will also be summarised categorically, in increments of 1 °C from ≥ 38 °C to ≤ 32 °C, as the proportion of individuals whose lowest core temperature during the trial intervention days was in each of these temperature bands. A binary definition of ‘compliance with cooling’ will constitute an AUC at least 72 degree × hours, this being at least half that theoretically achievable in the first 72 h. This definition will be used to identify the per-protocol and as-treated populations.

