### Sample size, power and interim analysis schedule

The overall recruitment target was set at 500 participants from commencement in December 2010 and was slightly increased to 510 participants in September 2017 after blinded review of the combined proportion of patients with ‘consent withdrawn’ or ‘loss to follow-up’. A total of 511 patients were randomised before the conclusion of trial recruitment on 10 November 2017.

A study of fixed size with full compliance and follow-up would require 364 patients (182 in each of two treatment arms) to detect a 15% absolute increase from 50% to 65% in favourable neurological outcome at six months following injury (equivalent to a 30% relative improvement in risk) with slightly > 80% (82.8%) power, assuming a two-sided alpha of 0.05 and an uncorrected Chi square test. This postulated POLAR risk improvement from a baseline of 50% to 65% in treated patients is equivalent to an odds ratio of approximately 1.86.

The original POLAR trial sample size of 364 fully evaluable patients was appropriately inflated to a practically required target of 500 patients to maintain 80% power to find the anticipated beneficial effect of prophylactic hypothermia while accommodating anticipated losses to follow-up (5%) and non-compliance (cross-over from cooling to control and related losses, maximum 12%). Also incorporated was a much smaller (0.7%) inflation necessary to accommodate the originally anticipated interim analyses of both mortality and the proportion of unfavourable neurological outcomes using Haybittle-Peto 3SD group sequential boundaries at two recruitment points (one-quarter [*n* = 125] and one-half [*n* = 250]) [7].

Following the October 2015 publication of the EUROTHERM3235 study [6], the POLAR DSMC required a further substantial increase in interim monitoring, namely at increments of 50 patients from *n* = 300 to *n* = 450 inclusive. Ten of 11 planned interim analyses will be of both mortality and the proportion of unfavourable neurological outcomes, while at the penultimate (*n* = 450) assessment, short-term 28-day mortality alone will be assessed due to time constraints. These extra analyses implied a sample size inflationary requirement (4% - 0.7% = 3.3% extra) [44] which may be accommodated within the originally planned sample size, provided losses to follow-up and non-compliance remained below anticipated limits.

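### The cooling-intensity analysis sets hypothermia-arm categories formed after randomisation against all standard-care patients, so it can show differences of unknown direction even if cooling has no effect

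*SAP article*

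**What the plan says.** The section Dose effect / Intensity of cooling applies to hypothermia-arm patients only. Each "will be categorised according to the time after randomisation to first reach one of two core temperature thresholds", namely 35 °C and 34 °C. The groups are then fixed: "Cooling intensity categories are defined as never achieving hypothermia and tertiles of time in those reaching hypothermia". Primary and secondary outcomes in these groups "will be compared across categories and to standard care patients". The paragraph states no adjustment, no handling of early death, no restriction of the control arm and no caution against a causal reading. The heading Exploratory analyses comes later and names the as-treated, per-protocol and complier analyses, not this one.

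Three other places bear on it:

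- **Statistical analyses** expects the main cause of incomplete cooling to be alcohol or drugs confounding the assessment, "leading to inclusion of patients with impaired consciousness not due to severe TBI for whom ongoing cooling may be clinically unwarranted". It continues: "Other anticipated reasons include extracranial trauma and coincident haemorrhage for which cooling may be at least temporarily undesirable".
- **As-treated and per-protocol analyses** notes that early death or loss within 72 h "will by definition reduce the observed dose of cooling received by such patients". This is said of the area-under-curve dose only.
- **Sensitivity analyses** lists core temperature closest to randomisation among the baseline covariates for adjusted models.

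**The concern.** Whether and when a patient reaches 35 °C is known only after randomisation. By the SAP's own account, cooling received depends on things that also drive the six-month outcome. A patient who proves not to have a severe brain injury has a good outlook and may not be cooled further. A patient who bleeds or dies early has a poor one and may not be cooled either. The control arm keeps all such patients, because nobody in it is sorted. Each category is therefore a prognostically selected part of one arm set against the whole of the other.

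The tertiles have a further problem. A patient who starts colder reaches 35 °C sooner, so the time groups also sort on starting temperature, which the SAP treats as a covariate for outcome.

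At stake is the reading of a result headed as a dose effect. Differences caused by selection could be reported as benefit or harm of faster or deeper cooling, for the primary outcome as well as the secondary ones.

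**Working it through.** **The plan's own figure.** The SAP gives no figure for this analysis. Its design figure was reproduced first to confirm the inputs. With 182 per arm, 50% v 65%, two-sided 0.05 and an uncorrected chi-square test, power = Φ[(0.15·√182 − 1.96·√(2·0.575·0.425)) / √(0.25 + 0.2275)] = Φ[(2.024 − 1.370)/0.691] = Φ(0.946) = 82.8%, as stated.

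**Inputs from the SAP.** 511 randomised 1:1; 50% favourable in controls; 5% loss to follow-up; non-compliance at most 12%.

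**Assumed, because the SAP gives no value.**
- The share never reaching the threshold: 12%, borrowed from the non-compliance maximum, with 25% as a sensitivity case.
- The favourable rate in that group: 20% to 85%.
- No effect of cooling, so both arms are 50% favourable overall.

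**Arithmetic.** If a share f never reaches the threshold and has favourable rate p, the reachers have (0.50 − f·p)/(1 − f).

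- p = 85%: (0.50 − 0.12·0.85)/0.88 = 0.398/0.88 = 45.2%
- p = 70%: (0.50 − 0.12·0.70)/0.88 = 0.416/0.88 = 47.3%
- p = 20%: (0.50 − 0.12·0.20)/0.88 = 0.476/0.88 = 54.1%
- 6% at 85% and 6% at 20%: never-reached group 0.063/0.12 = 52.5%; reachers (0.50 − 0.063)/0.88 = 49.7%
- f = 25%, p = 85%: (0.50 − 0.2125)/0.75 = 38.3%

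**Simulation of the same cases.** There were 3,000 trials per case, with arms of 255 and 256 less 5%. Cooling speed was unrelated to prognosis. Each comparison used an uncorrected chi-square test at 0.05. The last four columns give the share of trials that reject although cooling does nothing.

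| Never-reached group (assumed) | Never, favourable | Reachers, favourable | Never v control | All reachers v control | Across four categories | Arms as randomised |
|---|---|---|---|---|---|---|
| 12% at 50% (no selection) | 50% | 50% | 4% | 5% | 4% | 4.5% |
| 12% at 85% | 85% | 45% | 97% | 17% | 96% | 4.1% |
| 12% at 70% | 70% | 47% | 54% | 10% | 47% | 4.9% |
| 12% at 20% | 20% | 54% | 89% | 15% | 86% | 4.7% |
| 6% at 85%, 6% at 20% | 53% | 50% | 6% | 5% | 6% | 4.6% |
| 25% at 85% | 85% | 38% | 100% | 66% | 100% | 5.4% |

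The comparison as randomised stays near 5% throughout. The category contrasts do so only when there is no selection or when opposing reasons balance. Separately, four category-versus-control tests with no selection at all gave at least one p < 0.05 in 17% of trials.

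**If cooling speed is related to prognosis.** Take the even mix and assume a correlation of 0.3 between worse prognosis and faster cooling. The tertiles, fast to slow, become 37%, 50% and 63% favourable, and the test across categories rejects in 76% of trials. With 12% at 85% and the correlation reversed, they become 58%, 45% and 32%. The SAP gives no basis for either value.

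**The case against.** Several points on the other side are sound.

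**Direction.** A reader might infer that never-cooled patients will appear to do better than controls and cooled patients worse, because intoxication is named as the main reason for incomplete cooling. The document does not support that. It also names extracranial trauma and haemorrhage, which push the other way, and the cases above show that the sign can reverse or the bias nearly vanish. Nor is stopping cooling the same as never reaching 35 °C: some patients without severe brain injury will have crossed the threshold before cooling stops, so they enter the never-reached group only in part.

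**Gradient across tertiles.** A reader might also infer a false trend from fast to slow cooling. Suppose 5–15% of the arm lack severe injury (80–90% favourable), 80% of them are stopped within 0.5–6 h, 6% die early, and median time to 35 °C is 3.5 h and independent of prognosis. The trend is then about 1 to 4 points. With 255 × 0.88 / 3 ≈ 75 patients per tertile, the standard error of a difference is √(2 × 0.25/75) ≈ 8 points, so the trend is at most half a standard error. A large trend needs an assumed link between speed and prognosis.

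**Consequence.** The SAP calls all secondary outcomes hypothesis-generating, rests the trial's conclusions on the intention-to-treat primary analysis, and already plans an instrumental-variable estimate. It would be wrong to read this point as a threat to the main result.

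What the objection does not remove is that the contrast with standard care is specified without adjustment or caution, under a dose-effect heading, and for the primary outcome too.

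**Conclusion.** The point stands as a defect of specification. The contrast between cooling-intensity categories and standard care is not protected by randomisation, and the SAP's own account of why cooling is incomplete makes prognostic selection expected. It can show differences when cooling does nothing.

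Direction and size are unknown. Under the assumed inputs (12% never reaching the threshold, 50% favourable overall), reachers range from about 45% to about 54% against 50% in controls, and an even mix of reasons leaves almost no bias. These figures illustrate what could happen and do not forecast the trial's result. The primary conclusion is unaffected. The change should be made, but the trial's main inference does not depend on it.

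**What to change.** 1. In Dose effect / Intensity of cooling, remove the comparison of categories with standard-care patients.
2. Report the categories within the hypothermia arm only, adjusted for the baseline covariates already listed under Sensitivity analyses, including core temperature near randomisation. Show baseline prognosis and early deaths for each category. Adjustment will not remove selection by later events such as bleeding or death, so the text should say so.
3. Move this analysis under Exploratory analyses and label it non-causal.
4. Take any statement about the effect of cooling received versus control from the instrumental-variable complier analysis, which already covers binary and continuous compliance.
5. If a contrast with control is kept, restrict both arms to patients retrospectively confirmed to have severe TBI, as the per-protocol subset does. Label it exploratory and still open to selection through bleeding and early death.

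A landmark limited to patients alive and still on protocol is not a remedy, because it selects again on events after randomisation.

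The cost is wording and modest programming. Collection of six-month outcomes was still under way when the SAP was written. The loss is a direct category-versus-control contrast; the complier analysis as planned covers the primary outcome, so secondary outcomes would have no equivalent. The interaction analyses by Marshall class in the same section are outside this point.

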#### Sensitivity analyses of the primary and secondary outcomes

Sensitivity analyses of the primary and secondary outcomes will be performed using regression models adjusting for pre-specified baseline covariates as well as any covariate exhibiting substantial imbalance between randomisation arms, as recommended [37]. Linear and generalised linear model diagnostics, outlier assessment and remedial measures will follow standard approaches [30, 38].

Proportionality in ordinal logistic regression models will be assessed [39]. Also, the proportional hazards assumption across treatment arms in time-to-event analyses will be evaluated using scaled Schoenfeld residuals [40] and visual assessment of log-log plots.

Baseline variables to be included as fixed effects when developing adjusted outcomes models comprise the following:Geographic region (Australia and New Zealand, Middle East, Europe – three level nominal categorical)Age (integer values centred on overall median age of trial patients)GCS (integer values with a possible range of 3–15)Pupil reactivity (ordinal, three levels)Hypoxia (binary)Hypotension (binary)Marshall CT brain scan classification (nominal categorical, six levels) [39]Core temperature closest to time of randomisation (continuous)

Generalised linear mixed regression models will be applied with the same fixed effects covariate set while also incorporating as a random effect the multiple randomisation strata comprising hospital and pre-hospital research groups. In the event the above regression models do not accommodate the number of pre-specified covariates, sensitivity analyses will be simplified to adjust at least for POLAR treatment and the baseline extended IMPACT TBI probability of 6 month unfavourable outcome.

#### Exploratory analyses

It is well understood that trial protocols may not have been followed fully for some trial participants [17]. The intervention under examination is hypothermia to a target of 33 °C core temperature initiated within 3 h of injury and continued for at least 72 h, with rewarming guided by an intracranial pressure < 20 mmHg. Beyond the main ITT analyses of the primary and secondary outcomes, pre-specified exploratory analyses will use ‘as-treated’ and ‘per-protocol’ comparison approaches as well as methods to estimate the ‘complier average causal effect’ (CACE) of cooling [22, 38].

##### As-treated and per-protocol analyses

POLAR will repeat the primary and secondary trial outcomes in two pre-defined exploratory analysis sets: (1) the subset of compliant patients assigned to cooling compared to all patients assigned to the control (‘per-protocol’ analysis); and (2) according to the actual treatment received (‘as-treated’ analysis) [7].

The per-protocol analysis subset will comprise control and intervention patients who are demonstrated retrospectively to have suffered a severe TBI, thus excluding those with initially low GCS < 9 not due to severe head injury but rather associated with transient influences, such as alcohol or drug effects.

For analytic purposes, the differential ‘dose’ of early cooling received by each patient will be summarised as the area (degree × hours) under the protocol-defined cooling baseline value of 35 °C within 72 h of randomisation. Each individual’s AUC will be estimated by the linear trapezoidal method [41] applied to temperature data ignoring missing values. Early death or loss to follow-up within 72 h of randomisation will by definition reduce the observed dose of cooling received by such patients. The intensity of cooling will also be summarised categorically, in increments of 1 °C from ≥ 38 °C to ≤ 32 °C, as the proportion of individuals whose lowest core temperature during the trial intervention days was in each of these temperature bands. A binary definition of ‘compliance with cooling’ will constitute an AUC at least 72 degree × hours, this being at least half that theoretically achievable in the first 72 h. This definition will be used to identify the per-protocol and as-treated populations.

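### The per-protocol set is described in two ways that cannot both hold, and the wording that keeps all controls filters only the cooling arm, with bias of unknown direction

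*SAP article*

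**What the plan says.** The section 'As-treated and per-protocol analyses' makes three statements about the set.

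- The opening sentence gives the comparison as "the subset of compliant patients assigned to cooling compared to all patients assigned to the control".
- The next paragraph says: "The per-protocol analysis subset will comprise control and intervention patients who are demonstrated retrospectively to have suffered a severe TBI". Patients whose low GCS had a transient cause such as alcohol or drugs are excluded. Compliance is not mentioned.
- The last paragraph fixes the cut-off: "A binary definition of ‘compliance with cooling’ will constitute an AUC at least 72 degree × hours", justified as "this being at least half that theoretically achievable in the first 72 h". It adds: "This definition will be used to identify the per-protocol and as-treated populations". It also notes that death or loss to follow-up within 72 h lowers the recorded dose by definition.

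The section 'Statistical analyses' expects that "the main reason for incomplete compliance with cooling will be due to the effects of alcohol or other drugs", which brings in patients without severe TBI. It names extracranial trauma and coincident haemorrhage as other reasons. The sample size section allows at most 12% for cross-over from cooling to control and related losses. 'Exploratory analyses' classes the per-protocol work as exploratory, and the plan bases the trial's conclusions on the ITT primary analysis.

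**The concern.** A control patient found afterwards not to have had a severe TBI belongs to the set under the opening sentence and is excluded under the next paragraph. The section does not say which rule prevails or how they combine, so two analysts could build different sets, or the choice could be made once results are known.

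The opening sentence also has a fault of its own. Compliance is observed after randomisation and is required only in the cooling arm. The control arm holds patients who would equally have failed to comply had they been assigned cooling, and they all stay. The two groups then differ in prognosis even if cooling does nothing. The per-protocol analysis repeats the primary and all secondary outcomes, and the plan expects incomplete adherence, so readers are likely to look at it.

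**Working it through.** **1. The plan's own figure.** The dose is the area "under the protocol-defined cooling baseline value of 35 °C within 72 h of randomisation", and the intervention is "hypothermia to a target of 33 °C core temperature initiated within 3 h of injury". The theoretical maximum is (35 − 33) × 72 = 144 degree-hours, and half of that is 72. The stated cut-off reproduces.

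**2. What the cut-off implies.** At 33 °C, reaching 72 degree-hours takes 72 / 2 = 36 h. At a constant 34 °C it takes 72 / 1 = 72 h. A cooling patient held at 33 °C who dies before 36 h therefore cannot count as compliant. A control patient who dies at the same time stays in the set under the opening sentence.

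**3. The statements side by side.**

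| Statement | Cooling arm | Control arm |
|---|---|---|
| Opening sentence, with the AUC cut-off defining compliance | AUC of at least 72 | everyone |
| Next paragraph | confirmed severe TBI | confirmed severe TBI |

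The cooling-arm rules can be combined. The control-arm rules cannot.

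**4. Size of the bias under the opening sentence.** Inputs:
- No true effect, with 50% favourable in each whole arm (the plan's baseline rate).
- A share q of the cooling arm is non-compliant. The base case is q = 12%, the plan's ceiling.
- A proportion f of non-compliers has a favourable outcome. The plan gives no value, so every f is an assumption.
- 250 randomised per arm (half the 500 target), so 250 × 0.88 = 220 remain in the cooling arm at q = 12%.

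Favourable rate among compliant cooling patients = (0.50 − q·f) / (1 − q), compared with 0.50 in all controls. The last column is the chance of rejecting a true null with a pooled z test at two-sided 0.05.

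| f (assumed) | Cooling rate at q = 12% | Spurious difference | False rejection |
|---|---|---|---|
| 0% | 0.500 / 0.88 = 56.8% | +6.8 points | 31% |
| 25% | 0.470 / 0.88 = 53.4% | +3.4 points | 11% |
| 50% | 0.440 / 0.88 = 50.0% | 0 | 5% |
| 75% | 0.410 / 0.88 = 46.6% | −3.4 points | 11% |
| 90% | 0.392 / 0.88 = 44.5% | −5.5 points | 22% |

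Over the same range of f, q = 5% gives −2.1 to +2.6 points and q = 20% gives −10.0 to +12.5 points. The bias vanishes only if non-compliers do as well as the whole arm.

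**5. Direction.** Intoxicated patients without severe TBI probably have a high f, and removing them counts against cooling. Patients with haemorrhage or major extracranial injury probably have a low f, and early deaths have f = 0, so removing these favours cooling. The plan names all three kinds and gives no proportions.

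**The case against.** The best defence is to read the section as a whole. The AUC cut-off only says what compliant means in the opening sentence, and the next paragraph adds a restriction on both arms. The intended set would then be confirmed severe TBI in both arms plus AUC compliance in the cooling arm. Patients without severe TBI leave both arms, and the main expected source of imbalance goes with them. Much of this stands. A reader might count three rival populations, but the cut-off makes an existing term operational and is not a third one. The opening sentence's inclusion of every control still resists the combined reading. That reading also keeps a one-arm compliance filter. As an illustration (assumed), if 5% of cooling patients with confirmed severe TBI die before 36 h, there is no true effect and the whole-arm rate is 50%, the cooling rate becomes 0.50 / 0.95 = 52.6%, a spurious benefit of 2.6 points.

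A reader might also infer that the analysis is bound to make hypothermia look harmful. That needs most non-compliers to be good-prognosis patients without severe TBI. The 12% covers cross-over and related losses without giving a cause, and the plan names poor-prognosis reasons as well.

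Nor can the choice of set alter the trial's formal conclusion, which rests on ITT. The CACE analysis uses randomised arm as the instrument in the first instance and does not use this filter.

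**Conclusion.** The point holds as an internal contradiction with a limited consequence. The two descriptions disagree on which controls belong to the set, and the wording that keeps all controls gives a comparison that is biased unless non-compliers happen to have the arm's average outcome. At the plan's 12% ceiling and a 50% favourable rate, the spurious difference lies between about −5.5 and +6.8 points for assumed favourable rates among non-compliers of 90% down to 0%. These figures apply to the opening sentence taken literally. The documents do not settle the sign, so neither spurious harm nor spurious benefit can be claimed in advance. Only the exploratory per-protocol results are affected. It should be corrected because the plan presents these sets as pre-defined, and at the time of writing it still expected final six-month outcome data by June 2018.

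**What to change.** - Delete the clause that makes the whole control arm the comparator.
- Define the per-protocol set as confirmed severe TBI in both arms, judged from data already recorded and blind to arm and outcome.
- Report that set without a compliance filter as the like-for-like comparison.
- If the AUC criterion is also applied, label that result survival-dependent and state one rule, applied equally to both arms, for deaths before the threshold can be reached. Requiring the cut-off to be met in cooling and not met in control is not enough: it looks symmetric, but early deaths pass automatically in control and fail in cooling.
- Rely on the planned CACE analysis for the effect in compliers.

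The cost is a short change of wording, a somewhat smaller control set and a little more analysis work. Blinded judgement of severe TBI is additional effort unless it is already arranged.

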##### Estimation of the average causal effect among patients complying with treatment

In trials with incomplete adherence to treatment, such as that anticipated in POLAR, the ITT comparison only provides an estimate of the causal effect of treatment assignment rather than an estimate of the causal effect of treatment actually received. CACE analyses will be conducted to estimate the average effect of cooling treatment on the primary outcome for patients who would comply with whichever cooling group they were assigned to, considering both the binary and continuous definitions of compliance with cooling [22, 38].

Estimation of the CACE will use an instrumental variables approach in the first instance, with a randomised arm as the instrument [42]. Alternatively, if compliance is a time-varying variable, estimation of the CACE will use longitudinal nested compliance class methods [43].

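### Cooled patients who die early cannot meet the 72 degree × hours compliance rule, which builds a survivor bias into the per-protocol and as-treated comparisons

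*SAP article*

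**What the plan says.** In the SAP article, section As-treated and per-protocol analyses, cooling dose is the area "under the protocol-defined cooling baseline value of 35 °C within 72 h of randomisation". The cut-off follows: "A binary definition of ‘compliance with cooling’ will constitute an AUC at least 72 degree × hours", justified as "this being at least half that theoretically achievable in the first 72 h". Its role is explicit: "This definition will be used to identify the per-protocol and as-treated populations". The same paragraph acknowledges that death or loss to follow-up within 72 h will "by definition reduce the observed dose of cooling received by such patients". It gives no landmark, no allowance for time alive and no rule for early deaths.

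That section also describes the per-protocol set in two ways. One sentence compares compliant cooled patients with every control patient. The next paragraph limits both arms to patients shown afterwards to have had severe TBI.

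The section on the average causal effect among compliers estimates the CACE with randomised arm as instrument, "considering both the binary and continuous definitions of compliance with cooling".

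**The concern.** Compliance is settled after randomisation, and partly by survival. Under Primary outcome, death is GOSE 1 and unfavourable, so the rule sorts cooled patients partly by the outcome itself. Controls face no such test: a control who dies at 20 h stays in the comparator, while a cooled patient who dies at 20 h at target leaves the cooled group.

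These analyses are meant to show what cooling does when it is delivered. As defined, part of any advantage they show would come from removing deaths from one side. Real early harm from cooling could be hidden or reversed. Mortality is affected most directly, since the plan repeats the secondary outcomes in these sets.

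**Working it through.** **Inputs from the SAP article.** Reference 35 °C, 72 h window and cut-off of 72 degree × hours (As-treated and per-protocol analyses). Intervention: "hypothermia to a target of 33 °C core temperature initiated within 3 h of injury and continued for at least 72 h" (Exploratory analyses). Control rate 50% favourable, design effect 15 points, non-compliance at most 12% (Sample size, power and interim analysis schedule).

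**Assumed, because the document does not give them.** Proportion d dying before the cut-off can be met: 3%, 5%, 10%. Induction: linear from 36 °C to 33 °C over R hours.

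**1. The plan's own figure.** (35 − 33) × 72 = 144 degree × hours; half is 72. The stated threshold is reproduced.

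**2. Earliest time to comply.** Held at 33 °C from time zero: 72 / 2 = 36 h. With a ramp, the area gained during induction is ½ × (2R/3) × 2 = 2R/3, so the time needed is R + (72 − 2R/3)/2 = 36 + 2R/3. For R = 4, 8, 12, 24 h this gives 38.7, 41.3, 44.0 and 52.0 h. (A patient held at 32 °C throughout would need 72 / 3 = 24 h.)

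**3. Bias with no true effect.** Both arms are 50% favourable, early deaths are equal in both arms, and there is no other non-compliance.

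- Compliant cooled patients: 0.5 / (1 − d)
- Per-protocol comparator, all controls: 0.5
- As-treated comparator, controls plus cooled early deaths: 0.5 / (1 + d)

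| d | Compliant cooled | Per-protocol difference | As-treated comparator | As-treated difference |
|---|---|---|---|---|
| 3% | 51.5% | +1.5 | 48.5% | +3.0 |
| 5% | 52.6% | +2.6 | 47.6% | +5.0 |
| 10% | 55.6% | +5.6 | 45.5% | +10.1 |

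Simulation with 255 per arm and 4000 runs agreed. At a nominal two-sided 5%, false-positive rates at d = 3 / 5 / 10% were about 6 / 10 / 23% per-protocol and 10 / 21 / 63% as-treated, against 4–5% for ITT.

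**4. If cooling harms.** Assume early death of 5% in controls and 10% on cooling, and 50% v 45% favourable (ITT −5 points). Compliant cooled patients: 0.45 / 0.90 = 50%. Per-protocol: 50 − 50 = 0. As-treated comparator: 0.50 / 1.10 = 45.5%, so the difference is about +4.5. The harm disappears in one analysis and changes sign in the other.

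**5. Patients without severe TBI.** Let a share g have no severe TBI, be non-compliant when cooled, and have 80% favourable outcome (g and the 80% are assumed); d = 5%.

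- g = 5%: compliant cooled (0.50 − 0.04) / 0.90 = 51.1%. Against all controls +1.1 points. Against severe-TBI controls, 0.46 / 0.95 = 48.4%, so +2.7.
- g = 12%: compliant cooled (0.50 − 0.096) / 0.83 = 48.7%. Against all controls −1.3 points. Against severe-TBI controls, 0.404 / 0.88 = 45.9%, so +2.8.

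In the second case the two per-protocol definitions give opposite signs. It is at the far end: 12% plus 5% exceeds the plan's 12% ceiling.

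**6. CACE.** With randomised arm as instrument, CACE = ITT difference / difference in compliance. With no effect the numerator is 0 for any d. In step 4 it is −5 / 0.90 = −5.6 points, so the harm is enlarged, not hidden. With ITT of ±5 and 95% compliance it is ±5.3. For partly cooled patients scored as unexposed: if all of the plan's 12% were partly cooled with half the effect (assumed), the inflation is (0.88 + 0.06) / 0.88 = 1.07.

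**The case against.** The plan labels these analyses exploratory, calls every secondary outcome hypothesis-generating, and rests its conclusions on the primary ITT analysis. It says openly that early death reduces dose. That limits the consequence but does not mend the definition.

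The early-death rates are assumptions. The plan caps non-compliance and related losses at 12% and expects alcohol or drug effects to be the main reason. Early deaths of 10% would leave only 2 points for that reason, so the top row is an upper end.

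A reader might also infer four stronger things that the document does not support:

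- *That CACE carries the same survivor bias.* It does not. Every patient stays in the randomised arm in the numerator, so CACE is zero when cooling does nothing. Its separate and smaller problem is scaling: cooled early deaths and partly cooled patients count as unexposed under the binary cut-off, which pushes the estimate away from zero in either direction.
- *That the per-protocol analysis must favour cooling overall.* Only the survivor component has that sign. Dropping good-prognosis intoxicated patients from the cooled arm alone works the other way (step 5).
- *That any death within 72 h means non-compliance.* Patients who die after about 36–52 h may already have met the cut-off.
- *That the intensity categories are distorted to the same degree.* They too depend on survival ("Cooling intensity categories are defined as never achieving hypothermia and tertiles of time in those reaching hypothermia"), but reaching 35 °C or 34 °C does not take 36 h, and no size can be put on it from the document.

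**Conclusion.** The point holds for the per-protocol and as-treated comparisons. The binary rule excludes cooled patients who die before about 36 h at target (38.7 to 52.0 h under the assumed ramps), and nothing in the plan offsets this. With no true effect the survivor component is about +1.5 to +5.6 points per-protocol and +3.0 to +10.1 points as-treated for assumed early death of 3% to 10%, against a design effect of 15 points. These figures assume equal early death in both arms and no other cause of non-compliance.

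The net per-protocol direction cannot be stated until the two definitions of that set are reconciled. CACE is outside the survivor-bias finding. Severity is moderate: the ITT result and the trial's conclusions are untouched, but two pre-specified analyses would be biased as written.

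**What to change.** - Keep the 72 degree × hours cut-off for patients alive at 72 h. For earlier deaths adopt one rule: cooled-arm patients still on assigned cooling at death count as compliant. With no true effect this returns both comparisons in step 3 to zero.
- Repeat the per-protocol and as-treated comparisons as a 72 h landmark applied to both arms.
- Reconcile the two per-protocol definitions and apply the severe-TBI restriction identically in both arms.
- Report the continuous-AUC CACE, which is already planned, ahead of the binary version.
- State in the text that compliance depends partly on survival, and in which direction that component acts.

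The cost is SAP wording and minor programming. The rule needs each early death's cooling status at death, to be taken from the trial's temperature and treatment records. The landmark version loses early deaths from both arms, does not address mortality before 72 h, and compares survivors only, so it is no longer a fully randomised comparison if cooling affects early death. It should stand beside the comparison using the early-death rule, not replace it.
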